**Safety endpoints**

Hepatotoxicity (ALT/AST > 3x ULN; hyperbilirubinemia), myalgia—muscle ache or weakness without creatine kinase (CPK) elevation, myositis—muscle symptoms with increased CPK levels (3-10)ULN, rhabdomyolysis—muscle symptoms with marked CPK elevation (typically substantially greater than 10 times the upper limit of normal [ULN]) and with creatinine elevation (usually with brown urine and urinary myoglobin), minor Bleeding (BARC bleeding type 1 and 2 or major Bleeding (BARC bleeding type 3 –5 ) will be safety endpoints observed during the hospital stay.

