**Exclusion criteria:**

Patients with documented significant liver disease/dysfunction (AST/ALT > 240), myopathy and rhabdomyolysis (CPK > 5x normal), allergy or intolerance to statins, allergy or intolerance to aspirin, patients taking the following medications: cyclosporine, HIV protease inhibitors, hepatitis C protease inhibitor, telaprevir, fibric acid derivatives (gemfibrozil), niacin, azole antifungals (itraconazole, ketoconazole) clarithromycin, and colchicine, prior statin use (within 30 days), prior aspirin use (within 30 days), history of active GI bleeding in past three months, coagulopathy, thrombocytopenia (Platelet count < 100000/ dl), pregnancy, active breastfeeding, patient unable to take oral or nasogastric medications will be excluded. The patients in altered mental status, shock, acute renal failure, acute coronary syndrome, sepsis, and ARDS at presentation will be excluded.

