**4.Examination**

|  | At admission |
| --- | --- |
| SBP |  |
| DBP |  |
| Respiratory rate |  |
| Pulse rate |  |
| Pulmonary rales |  |

5.**Spo2**

| At admission | | At discharge |
| --- | --- | --- |
| Without oxygen support | Oxygen support (face mask) |  |
|  |  |  |
| Duration of days with spo2<95% | |  |

6.**Treatment**

|  | Yes/no |
| --- | --- |
| Hydroxychloroquine |  |
| Ivermectin |  |
| Doxycyclin |  |
| Azithromycin |  |
| Remdisivir |  |
| Tocilizumab |  |
| Vit D |  |
| Vit C |  |
| Corticosteroid |  |
| LMWH |  |
| Proton pump inhibitor |  |
| Antibiotic |  |

7.**Oxygen therapy**

|  | START | | END | | Duration(days/hour |
| --- | --- | --- | --- | --- | --- |
|  | DATE | TIME (am/pm) | DATE | TIME(am/pm) |  |
| Nasal prongs |  |  |  |  |  |
| Facemask |  |  |  |  |  |
| NRM |  |  |  |  |  |
| HFNC alone |  |  |  |  |  |
| HFNC plus face mask |  |  |  |  |  |
| HFNC plus NRM |  |  |  |  |  |
| CPAP |  |  |  |  |  |
| Invasive ventilation |  |  |  |  |  |
| The total duration of oxygen therapy |  | | | |  |

8.**Investigation**

|  | At admission | 5^th^ day |  |
| --- | --- | --- | --- |
| RBS |  |  |  |
| HB |  |  |  |
| TLC |  |  |  |
| ESR |  |  |  |
| Platelet count |  |  |  |
| Total bilirubin |  |  |  |
| Direct bilirubin |  |  |  |
| AST/ALT |  |  |  |
| ALP |  |  |  |
| LDH |  |  |  |
| S. Creatinine |  |  |  |
| S. FERRITIN |  |  |  |
| Prothrombin time |  |  |  |
| D-dimer |  |  |  |
| CRP |  |  |  |
| BNP |  |  |  |
| Procalcitonin |  |  |  |
| Troponin I |  |  |  |
| CPK |  |  |  |

9.**Primary endpoint**

|  | Yes/no |
| --- | --- |
| In-hospital mortality |  |
| Duration of mechanical ventilation |  |
| Length of hospital stay | (duration) |
| ARDS |  |
| Shock |  |
| Acute kidney injury |  |
| Impaired consciousness |  |
| Delirium |  |
| Stupor |  |
| Coma |  |

10.**Safety endpoints**

|  | Yes/no |
| --- | --- |
| Hepatotoxicity |  |
| Major bleeding |  |
| Minor bleeding |  |
| Proximal muscle weakness |  |
| Myalgia |  |

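### The muscle safety categories leave CPK ranges unclassified, including above 10x ULN, and the liver and muscle endpoints overlap values allowed at entry with no new-onset condition

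*Protocol*

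**What the plan says.** The Safety endpoints section names three muscle events:

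- myalgia: "muscle ache or weakness without creatine kinase (CPK) elevation";
- myositis: "muscle symptoms with increased CPK levels (3-10)ULN";
- rhabdomyolysis: muscle symptoms with a marked CPK rise, "typically substantially greater than 10 times the upper limit of normal [ULN]) and with creatinine elevation".

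The liver event is "Hepatotoxicity (ALT/AST > 3x ULN; hyperbilirubinemia". All are noted over the hospital stay. None is tied to the admission value or to new onset.

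The Exclusion criteria keep out "myopathy and rhabdomyolysis (CPK > 5x normal") and "documented significant liver disease/dysfunction (AST/ALT > 240"). Patients at or below those limits may enter.

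The proforma (Appendix-I) lists myalgia among the COVID-19 symptoms in item 3 and again among the safety endpoints in item 10. Item 10 also has "Proximal muscle weakness", hepatotoxicity and two bleeding rows, but no row for myositis or rhabdomyolysis. Item 8 records AST/ALT, creatinine and CPK. The Investigation section has liver tests, renal tests and CPK done at admission, on day 5 and at discharge. The Statistical Analysis section compares safety outcomes between groups by chi-square or Fisher's exact test.

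**The concern.** Safety of the triple therapy is one of the protocol's two objectives, and the regimen contains a statin. The liver and muscle endpoints are therefore a central part of the safety comparison. Two features of their definitions weaken them.

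First, the muscle categories read as a severity scale but do not join up. The gap above 10x ULN is the more serious one, because a larger CPK rise can go without a label while a smaller one receives it.

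Second, the values allowed at entry overlap the values that define an event. If admission findings are counted, the event tables mix presenting illness with what happened on treatment.

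The trial is open-label and those evaluating outcomes know the allocation (Blinding section), so unclear category boundaries also leave room for judgement that could differ by arm.

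**Working it through.** The plan gives no figure to reproduce. The check sets the thresholds side by side.

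**1. Muscle categories.** Each combination below assumes muscle symptoms are present. *Normal* in the Exclusion criteria is read as the ULN.

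| CPK (x ULN) | Creatinine not raised | Creatinine raised | Eligible on CPK at entry |
|---|---|---|---|
| 0.8 | myalgia | myalgia | yes |
| 2 | none | none | yes |
| 4 | myositis | myositis | yes |
| 5 | myositis | myositis | yes |
| 8 | myositis | myositis | no |
| 12 | none | rhabdomyolysis | no |
| 40 | none | rhabdomyolysis | no |

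Two gaps follow: above 1x and below 3x, whatever the creatinine; and above 10x with creatinine not raised. Values just above 10x are also uncertain when creatinine is raised, because the rhabdomyolysis wording gives a typical level and not a limit. A CPK rise without symptoms meets no category either, but that follows from a symptom-based scheme and is not counted here as a gap.

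**2. CPK at entry against the endpoint.** Entry is allowed up to 5x and myositis starts at 3x. A patient with CPK of 3x to 5x and muscle symptoms at admission is eligible and already fits the definition.

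**3. Myalgia.** A patient admitted with muscle ache and normal CPK already fits the myalgia endpoint.

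**4. Transaminases at entry against the endpoint.** The ranges overlap when 3 x ULN < 240, that is, when ULN < 240/3 = 80. The protocol does not state the ULN, so a range of assumed values is shown:

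| Assumed ULN | Endpoint starts above | Eligible and already an event |
|---|---|---|
| 30 | 90 | above 90 to 240 |
| 40 | 120 | above 120 to 240 |
| 50 | 150 | above 150 to 240 |
| 60 | 180 | above 180 to 240 |
| 80 | 240 | none |

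**5. Direction of the effect if admission findings are counted.** Let q be the share meeting an endpoint at entry, the same in both arms on average, and r the new-onset rate among the rest. The counted rate is q + (1 - q)r. The difference between arms becomes (1 - q) times the true difference, and the ratio moves towards 1.

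The following is an illustration only, and every input is hypothetical. Take new-onset rates of 6% and 3% (ratio 2.0):

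- q = 5%: 10.7% against 7.85%, ratio 1.36;
- q = 10%: 15.4% against 12.7%, ratio 1.21;
- q = 20%: 24.8% against 22.4%, ratio 1.11.

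At q = 10% the absolute difference falls only from 3.0 to 2.7 percentage points. The documents supply neither q nor r.

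**The case against.** An entry limit and an event threshold answer different questions, so their difference is not in itself a contradiction. The protocol does not say that admission values count as events, and a rule for baseline abnormalities is often left to the SAP, which is not at hand. This stands. A reader might infer that presenting disease will be reported as drug toxicity, but the text permits that reading without requiring it.

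A reader might also infer that the most marked CPK rises disappear from the record. They do not. The proforma captures CPK and creatinine values, myalgia and proximal weakness, so such a case has no endpoint label but can be recovered. For the same reason the missing myositis and rhabdomyolysis rows are a lesser matter, provided someone is told how to derive those events.

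A third tempting reading is that a true doubling of risk would be reported as a ratio of about 1.2. That rests wholly on assumed entry prevalences and event rates. Nor do the documents show a systematic tilt between arms, since randomisation balances entry findings on average.

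None of this closes the gaps in the muscle categories. The creatinine condition is joined to the CPK condition, so the word *typically*, which qualifies the CPK level, does not bring a patient at 12x with normal creatinine into rhabdomyolysis. Nor does a possible SAP rule cure definitions that the protocol itself fixes.

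**Conclusion.** The point holds in two parts of different strength.

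The gaps in the muscle categories are certain on the text and need no assumption: symptomatic CPK above 1x and below 3x ULN, and above 10x ULN without raised creatinine, have no category.

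The overlap with entry values is also on the page, with conditions. The liver overlap needs a ULN below 80. The CPK overlap takes *normal* as the ULN. The muscle overlaps concern only patients with symptoms at admission. Because no new-onset or worsening condition is stated, such patients can meet an endpoint at randomisation. The likely consequence is dilution of the safety comparison and inflated event rates in both arms, and its size cannot be given from the documents.

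The analysis of in-hospital mortality is untouched. The wording should be corrected, but this is not a fatal flaw.

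**What to change.** - Make the CPK reporting categories contiguous for patients with muscle symptoms. Give a place to values above 1x and below 3x ULN and to values above 10x ULN without raised creatinine, and state a firm boundary at 10x.
- Count a liver or muscle safety endpoint only when it is new, or worse than the value or symptom recorded at admission. State how much of a rise counts as worsening for patients already above a threshold at entry.
- State the ULN used for AST/ALT and CPK.
- Reconcile the Exclusion criteria, the Safety endpoints and proforma item 10, so that myositis and rhabdomyolysis are either recorded in their own rows or derived by a written rule from symptoms, CPK and creatinine. Myalgia is a yes/no item at admission, so worsening needs one extra entry on the form. Muscle weakness is not in the admission symptom list and needs an admission entry too.

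The cost is some definition wording and a few form entries, since the laboratory values are already scheduled at admission, day 5 and discharge. The downside is fewer counted events. No entry limit or clinical cut-off needs to change for this.

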The current therapy for COVID-19 involves oxygen support, steroids like dexamethasone, anticoagulation with low molecular weight heparin, and antivirals like remdesivir. However, even with these therapeutic agents mortality is still higher in moderate and severe disease. In patients hospitalized with COVID-19, only dexamethasone has been found to reduce the mortality (5). These therapeutic agents or regimens are not either fully effective or sufficient to combat the complete pathophysiology of the disease.

There is a need for a drug or combination of drugs that can target every component of the pathophysiology of COVID-19. Such therapeutic regimens should be easily available, low cost, and with an established safety profile. There is no single agent which can target all these pathophysiologic substrates. Hence, we aim to evaluate the combination of commonly used cardiac medication (Aspirin, Atorvastatin, and Nicorandil) with anti-inflammatory, antithrombotic, immunomodulatory, and vasodilator properties as adjuvant therapy in covid- 19. Moreover, these drugs are already extensively used, well-tolerated, and having a good safety profile in the human population.

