**Method and Materials**

**Objectives**

To test whether triple therapy with aspirin, atorvastatin, and nicorandil is superior to usual care in SARS-CoV-2 infected patients in improving outcome.

To find out the safety of triple therapy in SARS-CoV-2 infected patients.

**Study Design**: Single-centre, prospective, two-arm parallel design, open-label randomized control superiority trial.

**Place of Study**: The study will be conducted at the covid centre of [name] Government Medical College Tanda Kangra, Himachal Pradesh India, converted into a dedicated COVID-19 management centre since August 2020.

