**Intervention groups**

**Intervention group**

Atorvastatin will be prescribed as 40mg starting dose followed by 40 mg oral tablets once daily for ten days or till hospital discharge whichever is later. Aspirin dose will be 325 starting dose followed by 75mg once daily for ten days or till hospital discharge whichever is later. Nicorandil will be given as 10 mg starting dose followed by 5mg twice daily for ten days or till hospital discharge whichever is later. In addition, all patients will receive symptomatic treatment with antipyretics, adequate hydration, anticoagulation with low molecular weight heparin, intravenous remdesivir, corticosteroids (intravenous dexamethasone for 5 days or more duration whenever indicated, if oxygen requirement increasing or inflammatory markers are raised), and oxygen support. Patients will receive treatment for comorbid conditions as per guidelines.

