**Follow-up**

All study participants will be prospectively followed up during the hospital stay or 10 days whichever is later. Patients will be evaluated telephonically post-discharge till ten days.

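### The safety endpoints are limited to the hospital stay, while study treatment and follow-up run to the later of discharge or day 10, so events on treatment after an early discharge are not counted.

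*Protocol*

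**What the plan says.** - **Objective.** The Objectives section names two aims, the second being "To find out the safety of triple therapy in SARS-CoV-2 infected patients".
- **Safety window.** The Safety endpoints section lists hepatotoxicity, myalgia, myositis, rhabdomyolysis, and minor and major bleeding on the BARC scale. It closes by stating that these "will be safety endpoints observed during the hospital stay".
- **Treatment period.** The Intervention group section gives the same end rule for each drug: atorvastatin "followed by 40 mg oral tablets once daily for ten days or till hospital discharge whichever is later", aspirin "followed by 75mg once daily for ten days or till hospital discharge whichever is later", and nicorandil "followed by 5mg twice daily for ten days or till hospital discharge whichever is later".
- **Follow-up.** The Follow-up section uses the same end point, the later of the hospital stay and 10 days, and adds: "Patients will be evaluated telephonically post-discharge till ten days". It does not say what is asked.
- **Laboratory tests.** The Investigation section repeats liver and renal function and CPK on day 5 and at discharge, with nothing afterwards.
- **Haemodynamics.** The Introduction credits the combination with "anti-inflammatory, antithrombotic, immunomodulatory, and vasodilator properties as adjuvant therapy". The proforma (Appendix I) has systolic and diastolic pressure in a single admission column, and its safety section has no hypotension item. Shock appears among the secondary outcomes.

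**The concern.** Treatment and follow-up share one end point and the safety endpoints have an earlier one. Followed as written, a bleed at home on day 8 in a patient still taking aspirin would not be a safety endpoint, even if the patient reported it on the planned call. One of the trial's two objectives would then rest on only part of the exposure period for patients who leave early.

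The window also ends at discharge or in-hospital death. Length of stay is a secondary outcome and in-hospital mortality is the primary outcome, so treatment may change both. The Statistical Analysis section compares safety outcomes by chi-square or Fisher's exact test, that is, as proportions of patients. If the arms are observed for different lengths of time, those proportions are not like for like.

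A smaller matter is that a vasodilator action is part of the rationale, yet the trial record has no place for blood pressure after admission.

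A later statistical analysis plan could not repair this alone. The protocol and its proforma fix the endpoint list, the window and the recorded fields, and events that are never recorded cannot be analysed.

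**Working it through.** The protocol states no figure for this point, so there is none to reproduce. The check sets the windows side by side and then applies simple arithmetic.

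**Step 1: the windows, for discharge alive on day d.**

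| Item | Ends at | Source |
|---|---|---|
| Study drugs | max(10, d) | Intervention group |
| Follow-up | max(10, d) | Follow-up |
| Safety endpoints | d | Safety endpoints |
| Last scheduled laboratory test | d | Investigation |

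**Step 2: treatment time outside the safety window.** Counting days from the start of treatment:

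- Days not covered = max(0, 10 − d).
- Share of treatment days not covered = max(0, 10 − d) / max(10, d).

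The protocol gives no expected stay, so d is an assumption, shown over a range:

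| Discharge day d | Days not covered | Share |
|---|---|---|
| 5 | 5 of 10 | 50% |
| 6 | 4 of 10 | 40% |
| 7 | 3 of 10 | 30% |
| 8 | 2 of 10 | 20% |
| 9 | 1 of 10 | 10% |
| 10 or later | 0 | 0% |

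**Step 3: what the planned telephone contact could recover.**

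- Bleeding and muscle symptoms can be asked about by telephone.
- Hepatotoxicity is defined by ALT/AST and bilirubin. Myositis and rhabdomyolysis need CPK, and rhabdomyolysis also needs creatinine. Without a test after discharge, none of these can be established.
- Myalgia is defined by the absence of CPK elevation. A muscle complaint reported after discharge can therefore be counted as a symptom, but not sorted into the protocol's categories.

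**Step 4: effect of a longer window.** If the window for bleeding and muscle symptoms ended at max(10, d), the days not covered would be max(10, d) − max(10, d) = 0 for every d. That matches exposure, but the window still varies between patients, because anyone staying beyond day 10 is watched for longer. A comparison over a fixed period needs a fixed end, such as randomisation to day 10. Death before day 10 would still cut observation short.

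**The case against.** The strongest reply is that follow-up to day 10 already exists and that the proforma is meant to hold safety information, so this is only a wording conflict. That is largely fair, and it is why the fix is cheap. It does not remove the point: the safety definition excludes events after discharge, and no safety question is tied to the call.

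Four stronger readings are tempting, and the documents do not support them.

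- **That early discharge makes the triple therapy look safer.** A shorter stay in the intervention arm would shorten its observation. But in-hospital death also closes the window, and the sample size assumes mortality falling from 20% to 15%. Fewer deaths could lengthen observation in that arm. The net direction is unknown.
- **That the lost events can be sized.** If mean stay fell from 8 to 7 days, in-hospital person-days would fall by 1 − 7/8 = 12.5%. Both stays are invented for illustration, and turning that figure into lost events needs a constant event rate, which nothing in the protocol supports.
- **That safety is measured for only two of the three drugs.** The endpoints are not assigned to single drugs. The protocol's own review attributes inhibition of platelet activation to nicorandil's nitric oxide action, so on its terms the bleeding endpoints bear on nicorandil too. What is missing is a haemodynamic endpoint.
- **That leaving out hypotension is a contradiction.** The protocol names a vasodilator property but nowhere names hypotension as an expected harm, so the gap is an inference from mechanism. Shock, acute kidney injury and impaired consciousness are compared as secondary outcomes and may catch some consequences. The accurate statement is that lesser hypotension has no field on the proforma.

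**Conclusion.** The point holds as a mismatch between sections. The safety endpoints close at discharge while study treatment and follow-up run to the later of discharge or day 10. The gap affects only patients discharged alive before day 10. On the assumed discharge days it ranges from 10% of a 10-day course (day 9) to 50% (day 5), and it is zero from day 10. How many patients are affected cannot be known from the protocol.

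The arms may also be compared over unequal periods, because discharge and death both end the window. This is a risk of bias of unknown sign and size.

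The missing hypotension record is a worthwhile addition, resting on the stated vasodilator property, and is secondary to the window.

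The primary outcome is not touched. The change should be made because a stated objective depends on it.

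**What to change.** 1. **Reconcile the sections.** Align Safety endpoints with Intervention group and Follow-up by counting bleeding and muscle-symptom events in both arms from randomisation to the later of discharge or day 10. This concerns measurement only and leaves treatment duration as it is.
2. **Script the call.** Use the same questions on bleeding and muscle symptoms in both arms at the telephone contact already planned, and add proforma fields for the answers and the event date.
3. **Fix the comparison period.** Compare the arms primarily from randomisation to day 10. Report in-hospital events after day 10 separately, and show deaths before day 10 alongside, since death still ends observation.
4. **Label the laboratory-defined endpoints.** State that hepatotoxicity, myositis and rhabdomyolysis are in-hospital only.
5. **Add haemodynamic fields.** Put a hypotension item and the lowest in-hospital blood pressure on the proforma, taken from routine charting.

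**Cost.** Protocol wording, a short call script and a few proforma rows, with no extra visit or blood test. The downside is that post-discharge events are self-reported by participants who know their allocation, to staff who also know it. They are less precise and open to differential reporting between arms, so they should be shown separately from in-hospital events. Laboratory-defined events after discharge would remain unmeasured.

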**Intervention groups**

**Intervention group**

Atorvastatin will be prescribed as 40mg starting dose followed by 40 mg oral tablets once daily for ten days or till hospital discharge whichever is later. Aspirin dose will be 325 starting dose followed by 75mg once daily for ten days or till hospital discharge whichever is later. Nicorandil will be given as 10 mg starting dose followed by 5mg twice daily for ten days or till hospital discharge whichever is later. In addition, all patients will receive symptomatic treatment with antipyretics, adequate hydration, anticoagulation with low molecular weight heparin, intravenous remdesivir, corticosteroids (intravenous dexamethasone for 5 days or more duration whenever indicated, if oxygen requirement increasing or inflammatory markers are raised), and oxygen support. Patients will receive treatment for comorbid conditions as per guidelines.

